##### Retention in Care

2.10.2.3

Retention in care will be assessed over the same 6‐month follow‐up period in both groups and measured based on participants' attendance at scheduled clinic visits and continuity of follow‐up care. This outcome will be used to evaluate ongoing engagement with HIV‐HBV care services.

#### Exploratory Outcomes

2.10.3

Exploratory analyzes will be conducted to identify sociodemographic, clinical, and behavioral factors associated with virological response. In addition, the relationships among changes in HIV–HBV‐related knowledge, medication adherence, retention in care, and virological outcomes will be examined using correlation and multivariable regression analyzes. All exploratory variables will be collected during the same follow‐up period and assessed at equivalent time points across both study groups.

### Intervention Implementation

2.11

Two hospitals with established HIV ART follow‐up services and pre‐identified eligible adults living with HIV will be included in the study. Because this is a pilot quasi‐experimental study, the hospitals will be purposively assigned to either the intervention or comparison group based on service capacity, logistical feasibility, and the need to minimize contamination between study arms. One hospital will serve as the intervention site, where 60 participants will receive the patient‐centered education intervention in addition to routine ART care, while the other hospital will serve as the comparison site, where 60 participants will continue receiving standard HIV care. Thus, a total of 120 adults living with HIV will be enrolled in the study, with 60 participants in the intervention group and 60 participants in the comparison group (Figure 1).

**Figure 1 hsr273167-fig-0001:**
[figure not shown]
The CONSORT flow diagram of participant allocation, follow up, and analysis of effect of patient‐centered education on HIV virological suppression among unsuppressed adult people living with HIV‐HBV co‐infection in North‐West Ethiopia (*n* = 120).

#### Health Education Model for HIV VS

2.11.1

A framework for comprehending social behavior and personal cognition is provided by the Health Belief Model. Social psychologists first proposed it in the 1950s to elucidate the motivations underlying people's participation in health programs, such as vaccinations and physical examinations [25]. The Health Belief Model provides a framework for understanding social behavior and personal cognition, or an illness, and acceptance of particular health recommendations all of which are essential for improving health and reducing the difficulties of disease all influence their health‐related behaviors [26].

#### Components of the Health Education Model

2.11.2

The Health Belief Model (HBM) is a widely recognized theoretical framework used to explain health‐related behaviors by examining how individuals perceive health risks and respond to recommended preventive or treatment‐related actions. The model provides a useful framework for understanding social and cognitive factors that influence health behaviors and for designing interventions aimed at improving health outcomes and reducing disease‐related complications. In this study, the HBM serves as the conceptual framework for the patient‐centered education intervention.

The HBM proposes that an individual's likelihood of engaging in a health‐promoting behavior is influenced by several key constructs. These include perceived susceptibility, which refers to an individual's subjective perception of their risk of developing a disease or experiencing complications; perceived severity, which reflects beliefs about the seriousness and potential consequences of the condition; perceived benefits, which describe beliefs regarding the effectiveness of recommended actions in reducing disease risk or improving health outcomes; and perceived barriers, which represent perceived obstacles or challenges that may hinder adoption of the recommended behavior. The model also includes cues to action, which are internal or external triggers that motivate behavior change, and self‐efficacy, which refers to an individual's confidence in their ability to successfully perform the recommended health behaviors. Together, these constructs provide a framework for understanding and improving behaviors related to medication adherence, retention in care, and self‐management among adults living with HIV–HBV co‐infection (Figure 2).

**Figure 2 hsr273167-fig-0002:**
[figure not shown]
Inter‐relationship between variables of the health belief model, which will be used to explain HIV‐HBV co‐infected virological suppression improvement.

#### Procedure of the Health Education Intervention

2.11.3

After obtaining written informed consent, participants in the intervention group will complete a structured interviewer‐administered questionnaire to collect baseline data on socio‐demographic characteristics, clinical status, HIV‐HBV‐related knowledge, Health Belief Model (HBM) constructs, medication adherence, self‐management practices, and retention in care. Baseline clinical data, including HIV viral load, ART regimen, and relevant laboratory findings, will also be extracted from participants' medical records and laboratory reports.

Following baseline assessment, the patient‐centered health education intervention will be delivered to participants in the intervention group by trained healthcare professionals (HCPs), including nurses, pharmacists, and clinicians. The intervention will be conducted through face‐to‐face educational sessions in Amharic using standardized educational materials, PowerPoint presentations, interactive discussions, counseling sessions, and audiovisual teaching aids designed to enhance participant engagement and understanding.

The intervention will be delivered during routine ART follow‐up visits over a 6‐month period. Participants in the intervention group will receive structured monthly education and counseling sessions, with each session lasting approximately 40–60 min. Sessions will focus on HIV–HBV co‐infection, disease transmission, medication adherence, viral load monitoring, stigma reduction, self‐management practices, and behavioral strategies to improve retention in care. Family members or treatment supporters may participate in selected sessions, where appropriate, to strengthen social support and adherence.

Six trained healthcare professionals will implement the intervention at the designated intervention hospital. The intervention package, including educational content and delivery procedures, will be reviewed and validated by subject matter experts to ensure content accuracy, clarity, and consistency. To ensure intervention fidelity, all participants in the intervention group will receive the same educational content, dosage, frequency, and duration throughout the study period. Attendance will be documented, and participants who miss scheduled sessions will be contacted and rescheduled whenever feasible.

Outcome assessments will be conducted at two time points: baseline and at the end of the 6‐month follow‐up period. Changes in primary and secondary outcomes including HIV virological outcomes, medication adherence, HIV‐HBV‐related knowledge, self‐management practices, and retention in care will be compared between the intervention and comparison groups to evaluate the effectiveness of the patient‐centered education intervention.

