### Sample Size Determination

2.7

The sample size for this pilot quasi‐experimental study was determined based on the primary outcome, treated as a continuous variable (such as reduction in HIV viral load, adherence score, or knowledge score). Since measurements will be taken at baseline and endline in both intervention and comparison groups, the intervention effect will be evaluated by comparing mean changes in outcome between groups using a paired *t*‐test and a difference‐in‐differences approach [18].

The required sample size was calculated using the standard formula for comparing mean differences between two independent groups [19, 20].

The sample size for this study was determined using the formula for comparing two means: n = 2σ^2^(Z_a/2_ + Z_β_)^2^/Δ^2^

where (n) represents the required sample size per group, Z_a/2_ is the critical value corresponding to the desired significance level, (Z_β_) is the critical value corresponding to the desired statistical power, σ is the standard deviation of the change score, (σ^2^) is the variance of the change score, and Δ is the expected mean difference between the intervention and comparison groups. For this study, a significance level of 5% (α = 0.05) was assumed, corresponding to a critical value of (Z_a/2_ = 1.96), while a statistical power of 80% was used, corresponding to (Z_β_ = 0.84). The standard deviation of the change score was assumed to be 15, and the expected mean difference between the two groups was 8.4. Substituting these values into the formula gave; n = 2(15)^2^(1.96 + 0.84)^2^/8.4^2^

The variance was first calculated as (15^2^ = 225), and the sum of the Z‐values was (1.96 + 0.84 = 2.80), which when squared gave 7.84. Multiplying the numerator resulted in (2 × 225 × 7.84 = 3528), while the denominator was calculated as (8.4^2^ = 70.56). Dividing the numerator by the denominator gave (n = 3528/70.56 = 49.99), which was rounded up to 50 participants per group. To account for an anticipated 20% loss to follow‐up, the sample size was adjusted using the formula (n _adjusted_ = n/1–r), where (r) represents the expected attrition rate. Substituting the values yielded (n _adjusted_ = 50/0.80 = 62.5). For operational feasibility and balanced allocation, this was rounded to 60 participants per group. Therefore, the final sample size for the study was 120 participants, with 60 participants in each group.

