To estimate the adjusted intervention effect while accounting for repeated measurements within individuals and potential confounding, mixed‐effects linear regression models with random intercepts for participants will be fitted for each outcome. Fixed effects included group (intervention vs. comparison), time (baseline vs. endline), and the group‐by‐time interaction, with the interaction term representing the DiD estimate of the intervention effect. Models will adjust for clinically relevant covariates, including age, sex, religion, marital status, educational level, residence, WHO clinical stage, opportunistic infections, treatment interruption, alcohol use, smoking status, and condom use. Adjusted beta (β) coefficients with their corresponding 95% confidence intervals (CIs) were reported.

Model assumptions, including normality of residuals, linearity, homoscedasticity, independence of observations, and multicollinearity, were evaluated before model interpretation. Random‐effects assumptions will be assessed using the estimated variance components and intraclass correlation coefficient (ICC). All statistical tests were two‐sided, and statistical significance will be declared at *p* < 0.05.

Because this is a pilot quasi‐experimental study with a relatively small sample size, greater emphasis will placed on the magnitude and precision of the estimated intervention effects, expressed as adjusted β coefficients and 95% confidence intervals, rather than statistical significance alone. These findings are intended to inform the design and sample size estimation of future adequately powered randomized or multicenter intervention studies.

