This study has several methodological limitations. The intervention and control groups are recruited from only two health facilities, with one facility serving as the intervention site and the other as the control site. As a result, differences in outcomes may reflect not only the effect of the intervention but also underlying site‐specific characteristics, making it challenging to fully separate intervention effects from facility‐level influences. In addition, the inclusion of only two sites precludes the use of clustering‐adjusted analytical approaches such as mixed‐effects models or generalized estimating equations. Although multivariable analyzes will be performed to adjust for measured baseline differences between groups, residual confounding arising from unmeasured participant‐ or facility‐level factors may remain. Therefore, the study findings should be interpreted cautiously, taking into account the potential impact of unmeasured site‐specific influences.

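### Six providers deliver the education in one arm only, and the model has no provider term; if providers differ, the interval for the intervention effect is too narrow

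*Protocol article*

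**What the plan says.** Section 2.11 assigns one hospital and 60 participants to each arm. Section 2.11.3 states that "Six trained healthcare professionals will implement the intervention at the designated intervention hospital", and that sessions are given "by trained healthcare professionals (HCPs), including nurses, pharmacists, and clinicians". It also promises uniformity: "all participants in the intervention group will receive the same educational content, dosage, frequency, and duration throughout the study period". Attendance is to be documented. No section says how the 60 participants are divided among the six providers, or whether a participant sees the same provider each month.

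Sections 2.9.1 and 2.9.2 describe sessions adapted to the participant's needs and literacy, with individual counselling, goal setting and problem solving.

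Section 2.15 fixes the random-effects structure: "random intercepts for participants will be fitted for each outcome". The fixed effects are group, time and their interaction, and the interaction is the intervention effect. Independence of observations is among the assumptions to be checked. No provider term or design effect appears in section 2.7 or 2.15.

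The Discussion (section 3) treats clustering at hospital level only. It says "the inclusion of only two sites precludes the use of" clustering adjustments, naming mixed models and generalized estimating equations as examples, and concedes that site effects cannot be fully separated from the intervention.

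**The concern.** Counselling quality differs between people. Participants taught by the same six professionals share whatever those professionals do well or badly, and this happens in the intervention arm only (a partially nested design). With two time points, the participant random intercept cancels out of the change from baseline, so it cannot absorb a provider effect on that change. The model then treats the 60 changes in the intervention arm as independent.

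Interval width is what is at stake. Section 2.15 asks readers to weigh effect size and precision above the p value, and it offers the estimates as input to the design of larger studies. Those studies would use other providers, so uncertainty from having sampled only six belongs in the interval. The hospital-level argument in the Discussion does not cover this, because six providers exist inside one hospital.

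**Working it through.** **Inputs from the article.** Six providers (2.11.3); 60 enrolled per arm (2.11); in section 2.7, "a significance level of 5% (α = 0.05) was assumed", with 80% power, SD of change 15, difference 8.4 and 20% loss; two-sided tests (2.15).

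**Inputs assumed.** Provider ICC of the change score from 0 to 0.10; participants spread evenly over providers. The article gives neither.

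**The plan's own figure.** n = 2 × 15² × (1.96 + 0.84)² / 8.4² = 3528 / 70.56 = 50 per group, as stated. Inflation for loss gives 50 / 0.80 = 62.5, set to 60 in the article, which leaves 60 × 0.80 = 48 completers per group. No design effect enters.

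**Formulas.** With m participants per provider, the design effect in the intervention arm is DE = 1 + (m − 1) × ICC; in the comparison arm it is 1. True SE / model SE = √((1 + DE) / 2). Real two-sided error = 2 × (1 − Φ(1.96 / ratio)).

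Example, m = 60 / 6 = 10 and ICC 0.10: DE = 1 + 9 × 0.10 = 1.90; ratio = √(2.90 / 2) = 1.20; error = 2 × (1 − Φ(1.63)) = 10.4%.

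| ICC | SE ratio, m = 10 | Error, m = 10 | SE ratio, m = 8 (48 completers) | Power, m = 8 |
|---|---|---|---|---|
| 0 | 1.00 | 5.0% | 1.00 | 78.3% |
| 0.01 | 1.02 | 5.5% | 1.02 | 76.9% |
| 0.02 | 1.04 | 6.0% | 1.03 | 75.6% |
| 0.05 | 1.11 | 7.7% | 1.08 | 71.6% |
| 0.10 | 1.20 | 10.4% | 1.16 | 65.6% |

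The SE ratios do not depend on the outcome scale. The power column uses the SD of 15 and difference of 8.4 as given.

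**Simulation check.** 20,000 trials per setting, 48 per arm, six providers, ordinary two-sample test on change. The provider variance is the stated share of 15² in both patterns. In the rotating pattern, a provider is drawn at random for each of six sessions.

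| ICC | Error, one provider each | Error, rotating |
|---|---|---|
| 0 | 5.1% | 5.1% |
| 0.02 | 5.9% | 5.7% |
| 0.05 | 6.8% | 7.3% |
| 0.10 | 9.2% | 9.9% |

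Rotation does not help, because the arm mean still rests on the same six providers. It also makes the shared effect harder to see within the arm. At ICC 0.10 the simulated ratio of true to model SE was 3.57 / 2.99 = 1.20 with rotation and 3.55 / 3.04 = 1.17 without.

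**What a provider-based analysis can do.** In further simulation, a provider-level variance with small-sample degrees of freedom brought the error back to about 5%, but only when each participant had one provider. The provider variance estimate was zero or negative in 21% to 53% of trials for ICC 0.10 down to 0.01. With equal variances, the degrees of freedom are about (1 + 1)² / (1/5 + 1/47) = 18, which widens the interval by about 6% even if providers do not differ.

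**The case against.** A reader might infer that the model's standard error is simply wrong, or that each provider has ten participants of their own. The article supports neither. It gives no ICC and no rule tying participants to providers, and if inference is confined to these six providers, nothing is understated by this route. Three-day training, counselling guides and uniform content and dose all work to reduce provider variation, and the primary outcome is a laboratory value. These points favour the low end of the range, where the error rate is about 5.5%. They stand, and they make the conclusion conditional. They do not remove it, because uniform content does not make tailored counselling uniform, and the stated use in planning later studies reaches beyond these six people.

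A reader might also expect rotation among providers to shrink the problem. The simulation shows that it does not.

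The remedy has limits. Six providers estimate a variance poorly, and a term for the main provider captures little under rotation. This stands, and it argues for a supporting analysis rather than a new main model.

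The larger dependence is one hospital per arm. The Discussion says so, and no provider term touches it. Its sentence on precluded adjustment is about sites and makes no claim about providers, so it needs clarifying rather than correcting. It does not conflict with the mixed model in section 2.15, which handles repeated measures.

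Allocation details can be left to a fuller document. The random-effects structure, however, is fixed in the article.

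**Conclusion.** The point holds conditionally. Provider clustering arises in the intervention arm only, and nothing in the stated design or analysis handles it. If provider effects vary and the result is to apply beyond these six providers, the true standard error of the group-by-time effect is larger than the model's by about 2% at ICC 0.01, 8% to 11% at 0.05 and 16% to 20% at 0.10, and by nothing at ICC 0. The matching real error rates run from 5% to about 10%. The ICC range is an assumption. The size is similar with fixed and rotating providers. This is a moderate weakness in how precision will be reported, smaller than the acknowledged confounding of hospital with treatment and separate from it.

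**What to change.** - State how participants are allocated to providers, and record the delivering provider at each session in the attendance record that section 2.11.3 already plans.
- Keep the section 2.15 model. For each outcome add a supporting analysis. If participants mainly see one provider, add a provider-by-time random effect in the intervention arm only, with small-sample degrees of freedom. If they rotate, show the interval over a range of assumed provider ICC, for example 0 to 0.10.
- Where a provider variance is estimated, report it with its interval and call it imprecise.
- In the Discussion, make clear that the statement on precluded clustering adjustment refers to hospitals, and mention providers beside it as a further source of dependence.

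The cost is one field in the attendance record, one supporting analysis per outcome and a clarified sentence. The downside is somewhat wider supporting intervals, even where providers turn out not to differ, and a poorly estimated variance from six providers.

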### Data Collection Procedures

2.12

#### Baseline Survey

2.12.1

A baseline survey will be conducted prior to implementation of the intervention. Data will be collected through participant interviews and abstraction of clinical, laboratory, and patient medical records. Trained study nurses or research assistants will interview adult participants living with HIV–HBV co‐infection during enrollment using a structured questionnaire to collect socio‐demographic, clinical, behavioral, and HIV/HBV‐related information. Clinical and laboratory data, including HIV viral load, ART regimen, CD4 count, and other relevant medical information, will be extracted from participants' medical records and laboratory reports. In addition, Health Belief Model (HBM) constructs including perceived susceptibility, perceived severity, perceived benefits, perceived barriers, cues to action, and self‐efficacy as well as medication adherence and baseline knowledge regarding HIV–HBV co‐infection, will be assessed during the baseline evaluation.

#### Follow‐Up and Endline Survey

2.12.2

Data will be collected at two time points: baseline (enrollment) and at the end of the 6‐month follow‐up period. At both assessment points, trained research nurses will collect socio‐demographic, clinical, and behavioral information through participant interviews and abstraction of medical records. Information on clinic attendance, retention in care, and pharmacy medication refill history among participants receiving ART will also be obtained from patient medical records. HIV viral load data will be collected at baseline and at the scheduled 6‐month follow‐up visit using laboratory viral load testing reports or dried blood spot (DBS) samples, where applicable. In addition, data on medication adherence, Health Belief Model (HBM) constructs, self‐management practices, and HIV–HBV‐related knowledge will be collected using structured questionnaires. All primary, secondary, and exploratory outcome measures will be assessed using data collected at these two time points to enable comparison of changes over time between the intervention and comparison groups.

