### Sampling Method and Subject Recruitment

2.8

Because this is a pilot quasi‐experimental study, participants will not be randomly allocated to intervention and comparison groups. Instead, the selected hospitals will be purposively assigned to either the intervention or comparison group based on service capacity, logistical feasibility, and the need to minimize contamination between study arms. The University of Gondar Comprehensive Specialized Hospital will serve as the intervention site, where participants will receive the patient‐centered education intervention integrated into routine ART services, while Felege Hiwot Comprehensive Specialized Hospital will serve as the comparison site, where participants will continue receiving standard HIV care.

Within each study site, eligible participants will be selected using simple random sampling. After obtaining the necessary institutional permissions, a sampling frame consisting of all eligible adults living with HIV–HBV co‐infection receiving ART will be obtained from the respective hospitals. Each eligible participant will be assigned a unique identification number, and participants will be selected using a computer‐generated random number method until the required sample size for each study arm is reached.

Blinding of participants and intervention providers will not be feasible because of the nature of the educational intervention. Therefore, this study will be conducted as an open‐label trial. To minimize potential bias, standardized intervention delivery procedures, uniform data collection protocols, and structured outcome assessment tools will be used across both study sites. In addition, primary outcome assessments will rely primarily on objective clinical measures, including laboratory‐confirmed HIV viral load results and routinely documented medical records, whenever possible. Although the principal investigator and data analyst will be aware of group allocation, outcome assessment and data verification procedures will be standardized to reduce measurement and analytical bias.

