##### Medication Adherence

2.10.2.1

Medication adherence will be assessed at baseline and at the scheduled 6‐month follow‐up visit in both the intervention and comparison groups using a context‐adapted version of the Hill‐Bone Medication Adherence Scale (HBMAS) [23]. Medication adherence will be evaluated over the same 6‐month post‐enrollment follow‐up period used for assessment of the primary outcome, ensuring a comparable observation window across study arms.

The HBMAS is a validated self‐report instrument designed to assess adherence behaviors among individuals receiving long‐term therapy and has been adapted to capture adherence to ART and HBV‐active medications among adults living with HIV or HIV–HBV co‐infection [23, 24]. The adapted HBMAS assesses three domains of adherence: medication‐taking behavior, appointment keeping, and prescription refilling. Responses are recorded using a Likert‐type scale, and item scores are summed to generate a total adherence score, with higher scores indicating poorer adherence.

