#### Medication Adherence

2.12.5

Medication adherence will be assessed at baseline and at the end of the 6‐month follow‐up period using a context‐adapted version of the Hill‐Bone Medication Adherence Scale (HBMAS), a widely used, simple, and reliable self‐report instrument for evaluating adherence behaviors in chronic disease management. For this study, the scale has been adapted to assess adherence to ART and HBV‐active medications among adults living with HIV‐HBV co‐infection.

The adapted HBMAS evaluates three key adherence domains: medication‐taking behavior, appointment keeping, and prescription refilling, while maintaining the original conceptual framework of the instrument. Responses will be recorded using a Likert‐type scale, and item scores will be summed to generate a total adherence score, with higher total scores indicating poorer medication adherence.

Medication adherence will primarily be analyzed as a continuous outcome using the total HBMAS score to assess changes in adherence between baseline and the 6‐month follow‐up period. Mean changes in adherence scores between the intervention and comparison groups will be evaluated to estimate the effect of the patient‐centered education intervention. Additionally, adherence will be categorized as good or poor based on predefined cut‐off values derived from the total HBMAS score for supplementary categorical analyzes. Associations between the intervention and adherence status at follow‐up will be explored using appropriate regression models while adjusting for relevant baseline covariates. The adapted HBMAS has been widely used in clinical and research settings and is considered an appropriate tool for identifying varying levels of medication adherence in this study population [23, 24].

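### Adherence is judged only by a self-report scale in an open-label study that counsels adherence in one arm, and no adherence outcome or model uses the refill history being abstracted

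*Protocol article*

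**What the plan says.** All references are to the protocol article.

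- **Instrument.** Section 2.10.2.1 states: "The HBMAS is a validated self‐report instrument designed to assess adherence behaviors among individuals receiving long‐term therapy". The adapted version covers medication-taking, appointment keeping and prescription refilling, all summed into one score. Higher scores mean poorer adherence.
- **Analysis.** Section 2.12.5 states: "Medication adherence will primarily be analyzed as a continuous outcome using the total HBMAS score to assess changes in adherence". The supplementary categories use the same score: "adherence will be categorized as good or poor based on predefined cut‐off values derived from the total HBMAS score". Sections 2.1.2, 2.13.2 and 2.15 name no other adherence source.
- **Collection.** Section 2.12.2 says that at both time points "trained research nurses will collect socio‐demographic, clinical, and behavioral information", and it takes adherence from structured questionnaires. Section 2.11.3 includes adherence among the baseline items where "participants in the intervention group will complete a structured interviewer‐administered questionnaire to collect baseline data on". Section 2.12.2.1 describes interviewer administration in general terms.
- **Blinding.** Section 2.8 says "this study will be conducted as an open‐label trial", with one hospital per arm. It relies on objective measures and records to limit bias, but says so for primary outcome assessments.
- **Intervention.** Sections 2.9.1, 2.9.3 and 2.11.3 describe monthly education sessions over 6 months in the intervention arm, with adherence counselling as a component.
- **Refill data.** Section 2.12.2 adds that "pharmacy medication refill history among participants receiving ART will also be obtained from patient medical records". Section 2.12.2.1 lists pharmacy refill records again as a data source.

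**The concern.** The intervention teaches patients what good adherence is and encourages it for 6 months. Patients and providers know which programme they are in, and the hospital alone identifies the arm. Intervention patients may therefore describe their adherence more favourably at endline even if they take their medicines no differently. Comparison patients have no matching reason to change how they answer.

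Three results are exposed: the first-listed secondary outcome; the exploratory analysis relating changes in knowledge and adherence to virological response (2.1.3, 2.10.3); and the adherence adjustment of the viral load model that the abstract mentions. The study's Limitations section says that no baseline resistance testing was done, so adherence-related failure cannot be separated from resistance-related failure. That makes a credible adherence measure more valuable here. A second source, not dependent on what patients say, is already being abstracted, but the adherence outcome makes no use of it.

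**Working it through.** **Step 1. Does difference-in-differences remove the bias?** Write the reported score as the true score plus a reporting error *e*. Then

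reported DiD = true DiD + [(e_I,post − e_I,pre) − (e_C,post − e_C,pre)].

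A reporting error that stays constant within an arm cancels. An error that changes by *b* in the intervention arm only, after baseline, leaves reported DiD = true DiD + *b*. In the mixed model of 2.15 the group-by-time coefficient estimates this sum. Covariate adjustment does not separate the two parts, because none of the listed covariates measures reporting behaviour.

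**Step 2. Number analysed.** Section 2.7 computes n = 2 × 15² × (1.96 + 0.84)² / 8.4² = 3528 / 70.56 = 50 per group, which reproduces. It enrols 60 per group and expects 20% loss: 60 × 0.80 = 48 completers per group.

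**Step 3. Size of the effect under an assumed shift.** The documents give no figure for reporting bias, so the range for *b* is an assumption, in SDs of the change score. There is no true adherence effect. The test is a two-sample t-test on change scores, two-sided α = 0.05, with 2 × 48 − 2 = 94 degrees of freedom and critical value 1.986. The noncentrality is b × √(48/2) = 4.899 × b.

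| Assumed shift b (SD) | Noncentrality | Probability of p < 0.05 |
|---|---|---|
| 0 | 0 | 5% |
| 0.2 | 0.98 | 16.3% |
| 0.3 | 1.47 | 30.7% |
| 0.4 | 1.96 | 49.2% |
| 0.5 | 2.45 | 67.9% |

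A normal approximation gives 16.5%, 31.2%, 50.0% and 68.8%.

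**Step 4. Where could refill records enter?** The definitions, side by side:

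- Adherence (2.1.2, 2.10.2.1, 2.12.5, 2.13.2): HBMAS only. Its refilling domain is itself self-reported, so it is no independent check.
- Retention (2.1.2, 2.10.2.3): visit attendance, continuity of follow-up and routine monitoring. Refills are not named.
- Exploratory analyses (2.1.3, 2.10.3): refills are not named.
- Models (2.15): refills are not named. A treatment-interruption covariate is listed without a source.

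**Step 5. Would agreement in direction between two measures be enough?** With no true effect, and a refill estimate independent of the HBMAS error, the refill estimate points the same way half the time. False claims at shifts of 0.2 and 0.5 SD would fall only to 16.3% / 2 ≈ 8% and 67.9% / 2 ≈ 34%. Positive correlation between the two would make this worse. The size and interval of the refill estimate are needed, not just its sign.

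**The case against.** The strongest reply is that a scale described as validated is a legitimate choice for a secondary outcome in a pilot, and that the plan breaks no promise. Much of this stands, and several stronger readings should be set aside.

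- A reader might infer that the plan contradicts its own reliance on objective measures. It does not: section 2.8 states that safeguard for primary outcome assessments, and laboratory viral load meets it. The safeguard simply does not extend to adherence.
- A reader might infer that the refill data are used nowhere. The text does not show that. Section 2.12.2 mentions them alongside attendance and retention, so they may inform retention, and they could be the source of the treatment-interruption covariate. What can be said is that no adherence definition or model names them.
- A reader might infer that the endline HBMAS is certainly given by interview. Section 2.12.2 says structured questionnaires; the explicit statement that includes adherence is for the intervention group at baseline (2.11.3). The point needs only self-report by patients who know their programme.
- The 0.2 to 0.5 SD range is not from the documents, and the same table would apply to any unblinded self-report outcome. Section 2.15 also puts estimates and intervals ahead of significance. That softens the p-value illustration, but a biased estimate with a narrow interval is still biased.
- A derivation rule for refills could be left to a fuller document. The choice of adherence measure is different: the article fixes it in several sections, each time with the HBMAS alone.
- Refill coverage is not free of bias either. Monthly contact and rescheduling of missed sessions could raise possession in the intervention arm without changing ingestion.

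**Conclusion.** The point holds as a worthwhile, low-cost improvement to a secondary outcome. The adherence result rests on one self-report score, the design gives one arm a reason to report differently after baseline, and difference-in-differences cannot remove that. Under the assumed one-arm shift of 0.2 to 0.5 SD, no true effect and 48 completers per arm, the chance of a significant adherence difference is about 16% to 68%. These figures show sensitivity; they do not predict how much bias will occur. The primary comparison of viral load is not affected as a measurement. The adherence-to-virology analysis is affected, but the protocol labels it exploratory.

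**What to change.** In 2.10.2.1 and 2.15:

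1. Add a supportive refill-based adherence measure over the 6-month follow-up, for example proportion of days covered where dispensing dates and days supplied are recorded. Derive it by the same rule at both hospitals.
2. Report its between-group estimate and 95% CI beside the HBMAS result.
3. Use it alongside the HBMAS in the exploratory adherence-to-viral-load analysis.
4. State that an HBMAS difference which the refill measure does not support will be described as possibly due to reporting bias. Do not make agreement in direction alone the condition for claiming an effect.

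The cost is one derived variable and some wording; no extra visits or interviews are needed. Before committing, check that the abstraction form captures dispensing dates and days supplied, and that the records are complete and comparable at the two hospitals, because the documents do not say so. State the limits with the result: refills show possession and not ingestion, and monthly contact in the intervention arm may itself raise refill coverage.
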